##### Quality of life

Quality of life will be assessed by a 12-item Short-Form Health Survey (SF-12) (Table 4). The scale items include eight dimensions: general health (GH), physical functioning (PF), role physical (RP), body pain (BP), role emotional (RE), mental health (MH), vitality (Vt), and social function (SF). Scores will be calculated as percentages. The first four dimensions belong to the physical component summary (PCS) level, while the last four dimensions belong to the mental component summary (MCS) level. We will compare the quality of life and the value of each index between the two groups.

**Table 4 Tab4:** Twelve-item Short-Form Health Survey (SF-12)

Items	Score	Grading system
In general, would you say your health is?	1	Excellent
	2	Very good
	3	Good
	4	Fair
	5	Poor
The following two questions are about activities you might do during a typical day. Does your health now limit you in these activities? If so, how much?		
Moderate activities, such as moving a table, pushing a vacuum cleaner, bowling, or playing golf?	1	Yes, limited a lot
	2	Yes, limited a little
	3	No, not limited at all
Climbing several flights of stairs?	1	Yes, limited a lot
	2	Yes, limited a little
	3	No, not limited at all
During the past 4 weeks have you had any of the following problems with your work or other regular activities as a result of your physical health?		
Accomplished less than you would like?	1	Yes
	2	No
Are limited in the kind of work or other activities?	1	Yes
	2	No
During the past 4 weeks, have you been limited in the kind of work you do or other regular activities as a result of any emotional problems (such as feeling depressed or anxious)?		
Accomplished less than you would like?	1	Yes
	2	No
Cannot do work or other activities as carefully as usual?	1	Yes
	2	No
During the past 4 weeks, how much did pain interfere with your normal work (including both work outside the home and housework)?	1	Not at all
	2	A little bit
	3	Moderately
	4	Quite a bit
	5	Extremely
The next three questions are about how you feel and how things have been during the past 4 weeks. For each question, please give the one answer that comes closest to the way you have been feeling. How much of the time during the past 4 weeks?		
Have you felt calm and peaceful?	1	All of the time
	2	Most of the time
	3	A good bit of the time
	4	Some of the time
	5	A little of the time
	6	None of the time
Do you have a lot of energy?	1	All of the time
	2	Most of the time
	3	A good bit of the time
	4	Some of the time
	5	A little of the time
	6	None of the time
Have you felt downhearted and blue?	1	All of the time
	2	Most of the time
	3	A good bit of the time
	4	Some of the time
	5	A little of the time
	6	None of the time
During the past 4 weeks, how much of the time has your physical health or emotional problems interfered with your social activities (like visiting with friends, relatives, etc.)?	1	All of the time
	2	Most of the time
	3	A good bit of the time
	4	Some of the time
	5	A little of the time
	6	None of the time

### Safety outcomes

The following tests will be performed on all subjects during the study: physical examination (temperature, respiration, heart rate, blood pressure, height, and weight); gastroscope and biopsy; complete blood cell count; urinalysis; liver function (ALT, AST, alkaline phosphatase [ALP], serum total bilirubin [TBIL], and γ-glutamyl transpeptidase (γ-GT)); renal function (Cr, BUN) and glomerular filtration rate (GFR); and electrocardiography (ECG). In addition, a urine pregnancy test will be carried out for female patients of childbearing age.

### Participant timeline {13}

Table 5 shows the participant timeline.

**Table 5 Tab5:** Participant timeline

Visit in doctor’s office	Enrollment	Baseline	Post-allocation		Close-out
	Visit 1	Visit 2	Visit 3	Visit 4	Visit 5
Time point	-4W-0day	0day	4W±3day	12W±3day	24W±3day
Information collection					
Demographic information	×				
Physical examination	×		×	×	×
Informed consent	×				
Medical history	×				
Past history	×				
Concomitant treatment	×		×	×	×
Review selection	×				
Allocation		×			
Interventions					
Treatment group			×	×	×
Control group			×	×	×
Assessments					
Clinical sign and symptom score	×		×	×	×
Chinese medicine diagnosis	×				
Endoscope					
Kimura-Takemoto classification	×				×
Biopsy	×				×
13C or 14C breath test	×				
SF-12	×				×
Complete blood cell count	×				×
Liver function	×				×
Renal function	×				×
Urinalysis	×				×
ECG	×				×
Urine pregnancy test	×				
Adverse events			×	×	×
Efficacy determination					×
Others					
Drug distribution		×	×	×	
Drug recycling and count			×	×	×
Patient record card release		×			
Patient record card recycling					×
Check patient record card and conduct clinical evaluation			×	×	×
Summary					×

### Sample size {14}

The design is a randomized, double-blind, double-dummy, parallel-controlled, multicenter clinical trial. The sample ratio of the treatment group and the control group is 1:1. Based on the preliminary results of clinical research [8, 9], the expected efficacy of Elian Granules on chronic atrophic gastritis is 85%, with 63.3% of the therapeutic effect of Weifuchun used as the placebo effect. According to relevant references [16, 17] and the above data, two independent proportions superiority power analysis is used to estimate the sample size based on *α* = 0.05, *β* = 0.10, and power = 0.90 by Pass 11.0. It was estimated that no fewer than 95 subjects should be enrolled in each group. Allowing for a 20% drop-out, we, therefore, propose the recruitment of a total sample size of 220 patients. Referring to the phase II clinical trial, the planned total sample size is 240 cases in two groups. In terms of competition, each center should provide no fewer than 20 cases.

### Recruitment {15}

Recruitment of patients will take place in 9 tertiary hospitals and 1 secondary hospital in 6 provinces and cities in China, which can ensure the enrollment of sufficient subjects.

## Assignment of interventions: allocation

### Sequence generation {16a}

Central randomization and competitive enrollment will be used. SAS software will be used for randomization by providing the number of seeds and setting the block size to 4, thus generating the random arrangement table. Subjects will be competitively enrolled in 10 hospitals.

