### Intervention description {11a}

Elian Granules and placebo are produced by the Jiangyin Tianjiang Pharmaceutical Co. Ltd., China, for clinical research only (Approval No. 2006338). The placebo consists of 36% maltodextrin, 11% lemon yellow intermediate, 15% sunset yellow intermediate, 18% caramel intermediate, 4% bittering agent, 1% traditional Chinese medicine essence, and 10% lactose.

Although the placebo is similar to Elian Granules in color and smell, it is not the same. To make a blind test possible, all the drugs will be concealed in uniform, sealed, and opaque packages with the same labels that contain the drug name, the approval number of the pill, functions, usage, dosage, storage conditions, expiration dates for use, and the manufacturer’s name. The drugs will be administered by an independent clinical assistant in each center, who will take responsibility for the drug’s distribution, storage, and return. All drugs will be registered in the “drug-use record for clinical trials,” including information on the date of release of the trial drugs, the names of the subjects, and the quantities of drugs provided and retrieved. According to the intervention plan, there will be 6 medium packages contained in each large package and 112 small bags of drugs (12.1 g/bag) (Table 2) in each medium package. The patients will be randomly divided into the Elian Granules treatment group and the placebo control group. All drugs will be taken with hot water half an hour after meals, two small bags each time, twice a day for 24 weeks. Follow-up visits will be arranged at 4, 12, and 24 weeks after treatment. After the clinical study, the patients will receive routine treatment.

**Table 2 Tab2:** Components and dose of Elian Granules

Formula name	Chinese name	English name	Weight (g)	Weight (%)
Elian Granules	Ezhu	Zedoary turmeric	0.275	2.27
	Huanglian	Coptis	0.125	1.03
	Dangshen	Codonopsis	2.25	18.59
	Danshen	Salvia	0.8	6.61
	Danggui	Angelica	1.625	13.43
	Pugongying	Dandelion	1.475	12.19
	Baihuasheshecao	Oldenlandia diffusa	1.075	8.88
	Baizhu	Rhizoma atractylodis	1.65	13.64
	Shenggancao	Raw licorice	0.275	2.27
	Banxia	Pinellia	1	8.26
	Chenpi	Tangerine peel	0.55	4.55
	Fuling	Tuckahoe	1	8.26
	Total		12.1	100

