### Concealment mechanism {16b}

The random arrangement table generated by block randomization will be sealed as confidential data. According to the random arrangement table, the drugs are blinded by personnel unrelated to the trial, and the clinical research centers will administer the drugs according to the assigned drug number and the order of case selection. The blind code will be in triplicate and sealed in the office of the National Drug Clinical Trial Institution of Shuguang Hospital affiliated with Shanghai University of Traditional Chinese Medicine, Office of Clinical Trial Institution of Cooperation Unit and Statistical Unit. Each coded trial drug will have corresponding emergency letters, allowing to the blind be broken in the case of emergency. The emergency letters will be stored in each trial unit and collected at the end of the trial.

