### Procedure for unblinding if needed {17b}

Each drug number will be provided with an emergency letter, in which the corresponding drug group is sealed. In case of a medical emergency (for example, if the subject requires rescue), it can be opened. Should it be opened, the letter should be signed and dated by the reader, and the reason for opening will be recorded. In the event of an emergency, researchers and project leaders should attend and record the reason, time, and place of unblinding in detail and sign. The clinical trial team leader and the clinical supervisor will be informed timeously after unblinding. The case data will be kept intact. The emergency letter will be sent to each clinical research unit with the corresponding drug number and will be taken back after the trial.

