### Adverse event reporting and harms {22}

The safety of subjects during the study period is very important, and every adverse event will be recorded in detail on the adverse event form (AEF). Adverse events (AE) include any new disease, aggravation of the original disease, and complications related or unrelated to treatment. Any fatal, life-threatening, disabling, or serious event that results in hospitalization or long-term hospitalization will be considered to be an SAE. All these data will be recorded on the AEF along with the corresponding treatment methods and will be reported to the China Food and Drug Administration (CFDA), the Provincial Food and Drug Administration, and the ethics committee within 24 h. Adverse events will be reported to the other research centers at the same time. The severity of acute events will be divided into three grades: mild, moderate, and severe. A mild event represents a small amount of physical discomfort, with no intervention necessary, and having no effect on the study. Subjects experiencing severe events will, for their own safety, be withdrawn from the study. In the case of SAE, the researchers will be able to confirm the treatment allocation of the subjects through emergency unblinding. Any AE related to the trial drug will be treated free of charge. In addition, all adverse events will be recorded and tracked until they have been properly resolved or have stabilized. Any abnormal physical or chemical indices recorded after the medication will be reexamined to ensure that they return to normal or become stable.

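### A disclosed fixed block of 4, numbered dispensing and a placebo that is not identical leave later assignments open to prediction if sites hold consecutive drug numbers

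*Protocol article*

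**What the plan says.** - **Allocation.** Sequence generation {16a} states that "Central randomization and competitive enrollment will be used" and describes "setting the block size to 4, thus generating the random arrangement table". It does not say whether the list is stratified by centre or how numbers are divided among the 10 hospitals.
- **Dispensing.** Under Concealment mechanism {16b}, "the clinical research centers will administer the drugs according to the assigned drug number and the order of case selection". Procedure for unblinding {17b} adds that "The emergency letter will be sent to each clinical research unit with the corresponding drug number", so each site has a known set of numbers.
- **Product.** Intervention description {11a} concedes: "Although the placebo is similar to Elian Granules in color and smell, it is not the same". The measure it then gives is: "To make a blind test possible, all the drugs will be concealed in uniform, sealed, and opaque packages with the same labels". An independent assistant at each centre is responsible for distribution, storage and return.
- **Use.** "All drugs will be taken with hot water half an hour after meals, two small bags each time, twice a day for 24 weeks"
- **People.** Implementation {16c} has the site researchers both recruit and carry out the intervention. Section {17a} lists subjects, researchers and data analysts as blinded.
- **Opening the code.** {17b} ties this to a medical emergency. Adverse event reporting and harms {22} says: "In the case of SAE, the researchers will be able to confirm the treatment allocation of the subjects through emergency unblinding".

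**The concern.** A single fixed block of 4 does little harm while nobody can tell what earlier patients received. Here the protocol concedes a product difference and covers it with a package that hides dispensing but not use. Patients open the bags themselves and return at weeks 4, 12 and 24 to a team that is still recruiting. If a researcher forms a view of what recent patients are taking, a known block size turns that view into a forecast of the next assignment.

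What is at stake is selection bias. A recruiter who can forecast has some discretion over who enters and when: the exclusion of patients judged unsuitable or likely to be lost, and the interval of at least 2 weeks before consent. Patients with a better or worse outlook could then be steered towards one arm. The CMH test stratified by centre does not remove selection that happens within a centre.

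**Working it through.** The protocol gives no figure for predictability, so there is none to reproduce.

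**Inputs from the protocol:** block size 4, ratio 1:1, 10 sites, 240 patients, week-4 visit window ±3 days; 81 included by 16 July 2020, with completion expected around November 2022.
**Assumptions:** how numbers reach the sites (two cases below) and how accurately an earlier treatment is recognised (70% to 100%).

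**Case A: whole blocks held within a site, earlier treatments recognised without error.** A block has 6 equally likely orderings of AABB. The best guess is the arm with more places left.
- Position 1: 1/2.
- Position 2: one place is left in the arm already seen and two in the other, so 2/3.
- Position 3: with probability 1/3 the first two match and the next is certain; with probability 2/3 they differ and it is a coin toss. 1/3 × 1 + 2/3 × 1/2 = 2/3.
- Position 4: 1.
- Mean correct: (1/2 + 2/3 + 2/3 + 1)/4 = 17/24 = 70.8%, against 50% with no information.
- Certain in advance: (0 + 0 + 1/3 + 1)/4 = 33.3%, or 80 of 240 if this held at every site.

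**Case A with imperfect recognition, accuracy r.** Position 2 is r × 2/3 + (1 − r) × 1/3 = (1 + r)/3, and position 3 has the same value. Position 4 comes from enumerating all orderings and observations.

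| r | Pos. 1 | Pos. 2 | Pos. 3 | Pos. 4 | Mean |
|---|---|---|---|---|---|
| 0.7 | 0.500 | 0.567 | 0.567 | 0.616 | 56.2% |
| 0.8 | 0.500 | 0.600 | 0.600 | 0.704 | 60.1% |
| 0.9 | 0.500 | 0.633 | 0.633 | 0.828 | 64.9% |

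**Case B: one list interleaved at random over 10 sites, own patients recognised without error.** Each earlier member of a block is at the same site with probability 0.1. Knowing one or two earlier members gives 2/3 on average, a gain of 1/6; knowing all three gives certainty, a gain of 1/2.
- Position 2: 0.5 + 0.1/6 = 0.517.
- Position 3: 0.5 + 0.19/6 = 0.532.
- Position 4: 0.5 + 0.27/6 + 0.001/2 = 0.5455.
- Mean: 52.3%, with about 0.4% certain. A recruiter who simply guesses whichever arm is behind at the site, without using the numbers, reaches about 51%.

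**Does feedback arrive in time?** 240 − 81 = 159 patients over about 28 months at 10 sites: 28 × 30.4 × 10/159 = 53.5 days between patients at a site on average. That is later than the previous patient's week-4 visit (at most 31 days). It assumes even accrual, which competitive enrolment does not ensure.

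**Effect of varied blocks in Case A.** Simulation with 24 patients per site, perfect recognition, sizes 4, 6 and 8 chosen at random, and a guesser who tracks every block state consistent with the history: certain predictions fall from 33% to about 2.4%, but mean correct guessing falls only from 71% to 67%.

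**The case against.** The strongest objection is that the large figures need whole blocks within a site, while the protocol describes central randomisation with competitive enrolment and never says blocks are nested in centres. That stands. Numbered drugs and emergency letters at each unit are compatible with consecutive site-held numbers but do not establish them, and under interleaving the problem nearly disappears.

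Recognition is also assumed. The placebo contains colourants, a bittering agent and a herbal essence. Each patient takes only one product and has nothing to compare it with, and the recruiter would learn of it second-hand. That an independent assistant handles distribution and returns limits staff contact with opened product. These points lower the likely accuracy, but they do not stop a patient describing the product to a researcher.

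Entry at OLGA II or III needs agreement between two pathologists, which narrows the room for steering; the exclusion for unsuitability and the timing of consent remain discretionary.

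On opening the code, the adverse-event section also works through emergency unblinding, so its difference from {17b} is one of wording about when this applies. No SAE rate is given, so its effect on prediction cannot be sized.

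A reader might infer that sites can already predict a third of assignments, that the blind has failed, or that patients are being steered. The documents support none of these. Nor would varied block sizes alone cure the problem: they remove most of the certainty but little of the guessing.

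**Conclusion.** The weakness lies in a combination: a fixed, disclosed block of 4, numbered dispensing in enrolment order, and a conceded product difference for which only packaging is named as cover. Its size is conditional. With consecutive whole blocks at a site it reaches at most 33% certain and 71% correct, or 56% to 65% correct at an assumed recognition accuracy of 70% to 90%. With one list interleaved over the 10 sites it is about 51% to 52%, close to chance. The protocol does not state which arrangement applies, and recognition accuracy is unknown. Correction is worthwhile because it is cheap and removes the dependence on both unknowns; it is not evidence that the comparison is already biased.

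**What to change.** For patients not yet randomised:

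1. **Main remedy.** Have the central randomisation issue each kit by a scrambled, non-consecutive number, so that no centre dispenses a block in sequence, and state this in {16a} and {16b}.
2. Keep the block size for the remaining list out of the protocol and any other document the sites see.
3. Optionally, generate the unused part of the list with randomly varied block sizes (for example 4, 6 and 8), as an addition to item 1 and not in place of it.
4. Reword {11a} so that blinding does not rest on packaging alone, and acknowledge that the package no longer conceals the contents once opened.
5. Reconcile {17b} and {22} on when the code may be opened.

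The cost is a new seed and list for unused numbers, relabelling of kits not yet shipped, and protocol wording. No extra patients, visits or staff are needed. The downside is a slightly larger possible imbalance between arms within a centre. How many patients can still benefit depends on current accrual; 159 of 240 remained at the July 2020 count.

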### Concealment mechanism {16b}

The random arrangement table generated by block randomization will be sealed as confidential data. According to the random arrangement table, the drugs are blinded by personnel unrelated to the trial, and the clinical research centers will administer the drugs according to the assigned drug number and the order of case selection. The blind code will be in triplicate and sealed in the office of the National Drug Clinical Trial Institution of Shuguang Hospital affiliated with Shanghai University of Traditional Chinese Medicine, Office of Clinical Trial Institution of Cooperation Unit and Statistical Unit. Each coded trial drug will have corresponding emergency letters, allowing to the blind be broken in the case of emergency. The emergency letters will be stored in each trial unit and collected at the end of the trial.

### Implementation {16c}

The allocation sequence will be generated by a statistician independent of the data management statistical analysis performed in this trial. The recruitment and intervention of subjects will be completed by the researchers of this project in each clinical research center.

## Assignment of interventions: blinding

### Who will be blinded {17a}

Subjects, researchers, and data analysts will be blinded.

### Procedure for unblinding if needed {17b}

Each drug number will be provided with an emergency letter, in which the corresponding drug group is sealed. In case of a medical emergency (for example, if the subject requires rescue), it can be opened. Should it be opened, the letter should be signed and dated by the reader, and the reason for opening will be recorded. In the event of an emergency, researchers and project leaders should attend and record the reason, time, and place of unblinding in detail and sign. The clinical trial team leader and the clinical supervisor will be informed timeously after unblinding. The case data will be kept intact. The emergency letter will be sent to each clinical research unit with the corresponding drug number and will be taken back after the trial.

## Data collection and management

### Plans for assessment and collection of outcomes {18a}

The project will use electronic data capture (EDC) to collect and manage data and the REDCap system for synchronous data input. Before data entry, the data administrator will conduct EDC and REDCap system training to facilitate understanding of the overall situation, as well as mastering the data entry and export methods. The data manager and the principal researchers will work together to write the relevant documents, and the data manager will build and test the electronic case report form (eCRF). The supervisor will oversee the adherence of the trial to the trial plan and data entry, checking whether the data entry is synchronous, correct, complete, and consistent with the original data. Should errors and omissions occur, the researcher will be asked to correct them timeously. Only researchers and supervisors will have access to the subjects’ medical records, and they will sign a confidentiality agreement. Data managers, researchers, supervisors, and statisticians will conduct blind reviews and prepare a report on the quality of the data management. After the blind review and confirmation of the accuracy of the database, the database will be locked. After the data are locked, they will be handed over to the statisticians, and SAS 6.12 statistical analysis software will be used for statistical analysis in a semi-blind way, and the statistical analysis report will be written. After analysis, the medical records of the subjects will be kept in the data files of the drug clinical trial institution.

